### Interventions

Participants will either be subjected to an online CCT targeting working memory functioning (the adaptive PASAT) or a closely matched low cognitive load training. This allows to rule out motivational aspects of performing an adaptive computer task online. The tasks will be presented in-browser, using a Millisecond software Web license. Both training groups will be asked to perform 10 sessions of 400 trials (which takes 20 min per session at an average inter stimulus interval (ISI) of 3000 ms), providing similar learning experiences in both conditions. Prior to training, both groups will receive oral and written psycho-education concerning cognitive control training (based on the protocol of [17]) in order to enhance task engagement. This is important as previous work indicates that task engagement forms an important predictor of response to CCT [20]. Importantly, no explicit information will be given about the to be expected results. Furthermore, participants will receive an automated text message on a daily basis to prevent attrition during the training period (using SurveySignal software; [46]).

#### Cognitive control training condition

We will use an adaptive version of the PASAT [17, 18] to train participants’ cognitive control in the CCT condition. Participants will be presented with a continuous stream of auditory digits (1–9) and are instructed to immediately respond to the sum of the last two heard digits by clicking the corresponding response buttons (1–18). The speed of number presentation is adapted based on participants’ performance in order to train cognitive control in a frustrating task context. Participants begin each session with a 3000 ms ISI, which is reduced by 100 ms following every four consecutive correct responses, increasing task difficulty. Following every four incorrect responses the ISI increases with 100 ms, reducing task difficulty. Throughout each session participants are presented with their current ISI and amount of consecutive correct and incorrect responses. Participants’ responses and response times are being measured. In line with previous training studies the median ISI per session will be used as an indicator of ones performance during the training sessions.

#### Active control condition

In the active control condition, participants will be presented with a low cognitive load version of the adaptive PASAT. This training task shows high resemblance to the adaptive PASAT concerning stimuli, responses, modification of task difficulty, and evaluation of session performance. However, in this low cognitive load version of the adaptive PASAT participants are instructed to immediately respond to the last heard digit instead of mentally manipulating the content in working memory (i.e., instead of responding to the sum of the last two heard digits as in the CCT condition). To better resemble the response options of the adaptive PASAT, participants in the active control condition are presented auditory stimuli ranging from 1–18.

### Sample size

We are the first to explore effects of CCT targeting working memory functioning in a RMD sample which makes it impossible to provide an exact estimate of effect size for the main outcome measure in this sample. However, previous work on MDD patients has yielded an effect size of *ɳ*^*2*^ = .19 for brooding [20], whereas work with at-risk undergraduate students revealed an effect size of *ɳ*^*2*^ = .11 in confrontation with naturalistic stress [28]. Given that this study will use an at-risk sample (RMD), we will base estimations of sample size on the latter effect size. In order to be able to detect a similar effect over two time points with *α* = .05 and 1-β = .80, the total sample size should at least be 68 (*n* CCT = 34, *n* active control = 34). We will stop recruiting once 68 participants have entered the training phase.

### Randomization

Upon entering the study, participants will receive a sealed envelope containing an exterior subject number that will be used for registration purposes during the assessment sessions in the lab (baseline, post-training, and follow-up). The envelope will contain a training manual, an URL that directs participants to the online training task, and a personal training task identification code that should be used while performing the ten online training sessions at home. Prior to the study, an independent researcher will randomly link the training task identification codes to the subject numbers that will be used in the lab using an automated randomization program (RandList; randomisation.eu). This researcher will prepare the envelopes and keep a list of the linked subject numbers and training session identification codes in a locked closet at the office and a copy at home for safe keeping. Based on the training task identification codes, participants will either perform the CCT or low cognitive load training.

### Blinding

We present a double blind RCT design. Prior to the randomization procedure, the independent researcher will reset the online training task so that even-numbered training task identification codes will redirect the participants to one condition (CCT or active control), whereas odd-numbered training task identification codes will redirect the participants to the other condition. The researchers of this study will not be aware of the training task identification codes (these are randomly generated and presented in a sealed envelope) or the link between even- or odd-numbered identification codes and training condition. Furthermore, participants will be instructed not to share details concerning the content of the training task or the personal training task identification code with the researchers.

During data-analysis, the researchers will remain blind of training task condition by separating (a) analysis of training task performance and process measures (based on even- or odd-numbered training task identification codes) from (b) analysis of training effects on the outcome measures. Concerning the latter, the independent researcher will provide the researchers with a list grouping the subject numbers — used during the lab sessions — in two non-informative conditions following completion of data-collection. Importantly, at this point (lab) subject numbers will not be linked to the personal training task identification codes. This allows blind evaluation of training effects. The blinding will only be broken for the more explorative analyses linking training task process measures with the outcome measures. Furthermore, we will use the CEQ-data to check for successful blinding of participants.

### Analysis

In line with Consolidated Standards of Reporting Trials (CONSORT; [47]), we will use intention-to-treat (ITT) analysis to test effects of CCT on primary and secondary measures post-training and at follow-up. Missing data will be handled using the Last-Observation-Carried-Forward (LOCF) method. Effects of CCT will be tested using Repeated Measures, analysis of variance (ANOVA), or covariance (ANCOVA) with follow-up *t*-tests. Exploratory analysis will take into account potential moderators of training effects such as variability in baseline depressive symptomatology and cognitive control. ITT might not necessarily apply to the exploratory analyses such as analysis of process measures of training. As secondary analysis, we will also perform completers-only analyses. Explorative within-group mediation analysis will be performed using a stepwise regression approach [48] and the Preacher and Hayes [49] bootstrapping method.

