**Methods/design:**

We present a double blind randomized controlled design. Remitted depressed adults will complete 10 online sessions of a cognitive control training targeting working memory functioning or a low cognitive load training (active control condition) over a period of 14 days. Effects of training on primary outcome measures of rumination and depressive symptomatology will be assessed pre-post training and at three months follow-up, along with secondary outcome measure adaptive emotion regulation. Long-term effects of cognitive control training on broader indicators of functioning will be assessed at three months follow-up (secondary outcome measures).

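### LOCF as the only missing-data rule for the ITT analysis can bias the three-month effect in either direction and overstates the information observed

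*Protocol article*

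**What the plan says.** The Analysis section commits the trial to ITT: "we will use intention-to-treat (ITT) analysis to test effects of CCT on primary and secondary measures post-training and at follow-up". The rule for missing scores follows at once: "Missing data will be handled using the Last-Observation-Carried-Forward (LOCF) method". The tests are conventional: "Effects of CCT will be tested using Repeated Measures, analysis of variance (ANOVA), or covariance (ANCOVA", with t-tests to follow. One further analysis bears on missing data: "As secondary analysis, we will also perform completers-only analyses". No assumption about why data are missing is stated, and no likelihood-based model or multiple imputation is mentioned.

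Table 1 schedules RRS, BDI-II and CERQ at baseline, post-training (2 weeks) and three months. QLDS, WHODAS 2.0, RS and RDQ are scheduled at baseline and three months only. The abstract assigns the functioning measures to the last visit: "Long-term effects of cognitive control training on broader indicators of functioning will be assessed at three months follow-up (secondary outcome measures".

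**The concern.** LOCF replaces an unknown three-month score with an older one and then treats it as observed. The Discussion sets the aim as lower vulnerability over 3.5 months in people who enter in remission, so most of the change of interest falls after the carried-forward score was taken. For RRS and BDI-II the carried score is about three months old (lost after post-training) or older (lost before it). For the functioning measures every missing three-month score becomes a change of exactly zero.

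Two results are at stake. An effect that appears after training would be diluted. If one arm loses more participants while scores drift, a difference could appear where there is none. The training task is made demanding on purpose, "in order to train cognitive control in a frustrating task context", so unequal loss is possible. The direction of error cannot be known beforehand, so LOCF cannot be defended as conservative.

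**Working it through.** **The plan's own figure.** From η² = 0.11, f = √(0.11/0.89) = 0.352 and d = 2f = 0.703. The Sample size section works "with *α* = .05 and 1-β = .80"; a two-sided test is assumed here. With f rounded to 0.35, the noncentral t gives 34 per arm, N = 68, power 0.812. Unrounded f gives 33 per arm, N = 66. The stated 68 therefore reproduces, as a number with complete data.

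**Inputs.** From the article: 34 per arm, three visits, LOCF. Assumed, because the article does not give them: SD 1, correlations 0.7/0.6/0.7 between visits, dropout of 10% to 30%, half of it before and half after post-training and, in the rows below, unrelated to scores. Negative values favour CCT.

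**Expected LOCF mean.** For an arm with dropout p and true means μ1, μ2, μ3 at the three visits, the LOCF mean at three months is

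(1 − p)·μ3 + (p/2)·μ2 + (p/2)·μ1.

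The expected LOCF effect is this quantity in CCT minus control. It was checked by simulation (3,000 trials per row, three-month score regressed on arm and baseline):

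| Scenario (dropout control / CCT) | True effect | Formula | Simulated LOCF | Rejection rate |
|---|---|---|---|---|
| Both worsen 0.5 late, 20/20 | 0 | 0.40 − 0.40 = 0 | 0.007 | 5.0% |
| Same, 10/30 | 0 | 0.35 − 0.45 = −0.10 | −0.107 | 8.4% |
| Same, 30/10 | 0 | 0.45 − 0.35 = +0.10 | +0.107 | 8.4% |
| Late effect, 20/20 | −0.50 | 0 − 0.40 = −0.40 | −0.400 | 55% |
| Late effect, 10/10 | −0.50 | 0 − 0.45 = −0.45 | −0.447 | 63% |
| Early effect of −0.50 gone by three months, 20/20 | 0 | 0.1 × (−0.5) = −0.05 | −0.054 | 6.6% |
| Constant effect from post-training, 20/20 | −0.50 | −0.40 − 0.05 = −0.45 | −0.459 | 68% |

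In the last row complete data gave −0.510 in the same runs. For 10/20 with both arms worsening by 0.5, the formula gives 0.40 − 0.45 = −0.05. A separate simulation (all correlations 0.6, 4,000 trials) gave a false benefit of 0.05 SD with 5.7% rejection, and for 10/30 it gave 0.10 SD with 8.6%.

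**Functioning measures.** With no post-training score the mean is (1 − p)·μ3 + p·μ1. Equal dropout p then shrinks any effect to (1 − p) of its size, whenever it emerged: 20% lost at p = 0.20.

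**Standard error.** In the late-effect 20/20 scenario the LOCF model SE is 0.188. The sampling SD of a missing-at-random estimate is 0.213 and the completers-only SE is 0.219, so LOCF is lower by 1 − 0.188/0.213 = 12% and 1 − 0.188/0.219 = 14%. It is even below the 0.195 obtained with no missing data. It does match LOCF's own sampling SD (0.185).

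**Source of the type I error.** With bias b and SE 0.19, rejection is about Φ(−1.96 + b/SE) + Φ(−1.96 − b/SE). For b = 0.10 this is 0.076 + 0.006 = 8.2%, and for b = 0.05 it is 0.045 + 0.013 = 5.8%. Bias alone accounts for the inflation.

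**After the change.** In the late-effect scenario the missing-at-random estimate is −0.500 at 20% dropout, and −0.495 at 10%.

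**The case against.** - **Bias is not automatic.** A reader might infer that LOCF necessarily distorts the three-month effect. It does not: with equal dropout and the same course in both arms the bias is about zero and type I error is 5.0%. The higher figures need both unequal dropout and a general worsening, and the article gives neither. This stands.
- **The intervals are not simply too narrow.** A reader might also infer that LOCF confidence intervals are always too short. As an interval for what LOCF itself estimates, the width is right. The accurate statement is that the SE is small relative to the information observed. This stands.
- **Unequal dropout is only a possibility.** The control task is also adaptive and closely resembles CCT, daily reminders are sent during training, and payment follows the last visit. Stopping training need not mean missing a lab visit. This stands.
- **Recurrence is not an endpoint.** The MINI is given at baseline only and the primary outcomes are continuous scores, so the article does not support a claim that LOCF hides diagnosed relapses. At post-training, LOCF spans only about two weeks. This stands.
- **LOCF can do tolerably well.** With a constant effect from post-training it loses only about 10% (0.459 against 0.510) and rejects more often than completers-only (68% against 63%). That is true of this pattern, but the pattern cannot be assumed beforehand.
- **Completers-only is already planned.** It was unbiased in the scenarios above and would have revealed the discrepancy, so it is a partial check. It departs from ITT, however, and can be biased when dropout depends on post-training or unobserved scores. Dropout because of worsening was not quantified here.
- **An SAP may say more.** The article states the rule outright, so this is a fixed choice and not an omitted detail.

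**Conclusion.** The point holds in a limited form. LOCF is the sole stated rule for the ITT analysis of every primary and secondary outcome, and it is an inferior one for the three-month comparison. It can bias that comparison in either direction when dropout or trajectories differ between arms.

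Under the assumed inputs the false effect runs from about 0 to about 0.11 SD, with type I error between 5% and about 9%. A late-emerging effect loses about 20% at 20% dropout per arm, and power is 55%, against 60% for completers-only and 71% with complete data. These are illustrations over a range, not predictions, because no dropout rate or expected drift is given. Certain bias, and intervals that are too narrow in every case, are stronger claims that the documents do not support.

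The rule is still worth changing: its direction of error is unknown beforehand and a better analysis needs no new data.

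**What to change.** Replace LOCF as the primary rule with one of the following:

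- a likelihood-based mixed model for repeated measures with baseline as one of the responses, unstructured covariance and condition × time, so that every randomised participant stays in the analysis; or
- multiple imputation under missing at random, using all baseline and post-training scores.

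For QLDS, WHODAS 2.0, RS and RDQ, use baseline-adjusted ANCOVA with the same multiple imputation. Do not restrict the analysis to participants with a post-baseline score, since that drops randomised participants and departs from the ITT commitment.

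State the missing-at-random assumption and add one delta-adjusted sensitivity analysis in which missing scores are worse than predicted. Keep LOCF and completers-only as supportive analyses at most, and report dropout by arm and visit.

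Make the change before the independent researcher releases the list that groups participants by condition. It costs a little more analysis work and a somewhat larger, honest SE (about 0.213 in place of 0.188 in the late-effect scenario at 20% dropout). It needs no extra participants or visits.

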## Method

### Design

We present a 2 (Condition) x 3 (Time) double blind, randomized controlled design. Adult RMD participants will be randomly allocated to either an online CCT intervention targeting working memory functioning or a low cognitive load training (active control condition). Both groups will perform 10 online training sessions over a period of 14 days, flanked by pre- and post-training lab assessments. Participants will return to the lab for a final assessment at three months follow-up (see Fig. 1 for an overview of the design). This study has been approved by the local ethical committee of the Faculty of Psychology and Educational Sciences of Ghent University and was registered with ClinicalTrials.gov, number NCT02407652.

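### The plan lists repeated measures, ANOVA or ANCOVA and does not require the baseline score as a covariate for RRS and BDI-II; naming one baseline-adjusted model costs nothing and can add precision

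*Protocol article*

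**What the plan says.** The Analysis section commits to intention-to-treat testing of the primary and secondary measures at post-training and at follow-up. It then gives the method: "Effects of CCT will be tested using Repeated Measures, analysis of variance (ANOVA), or covariance (ANCOVA"), with t-tests to follow. It does not tie any listed method to RRS or BDI-II. Baseline depressive symptoms appear there only as a possible moderator in exploratory work, not as a covariate in the confirmatory test.

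Two other sections bear on the choice without settling it:

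- Design: "We present a 2 (Condition) x 3 (Time) double blind, randomized controlled design". The usual test for this layout is the Condition x Time interaction on 2 degrees of freedom.
- Sample size: the trial is sized to "detect a similar effect over two time points", an interaction on 1 degree of freedom. The two occasions are not named.

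Table 1 and the Procedure section show RRS, BDI-II and CERQ collected at baseline, post-training and 3 months, and QLDS, WHODAS 2.0, RS and RDQ at baseline and 3 months. Every outcome therefore has its own baseline score.

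**The concern.** The article states a method, and that method is a list joined by an or. The members of the list use the baseline differently. A two-time repeated-measures interaction treats baseline as an outcome and amounts to a test on change scores. An ANOVA of the later score ignores baseline. ANCOVA adjusts for it. With 34 participants per arm, these can give different standard errors and different p-values on the same data.

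Two things are at stake. The first is precision: two of the options use the baseline less efficiently than the third, though it is measured for everyone. The second is error control: if the test is settled only once results can be seen, the nominal 5% level no longer holds.

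**Working it through.** **Inputs.** From the Sample size section: eta-squared .11, alpha .05, power .80, total N = 68 in two arms of 34. The correlation rho between baseline and later score is not in the documents; I assume .5 to .8. I also assume equal SDs across arms and occasions and, for the three-time test, compound symmetry.

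**Step 1: reproduce the plan's figure.** f² = .11/.89 = .1236. For a two-group, two-time interaction, take noncentrality lambda = f²(N-2) = .1236 x 66 = 8.157 on F(1, 66). Power is .8035 at N = 68 and .791 at N = 66. The planned 68 is confirmed.

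**Step 2: variances, in units of the outcome variance.**

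- ANOVA of the later score: 1
- Two-time interaction (change score): 2(1-rho)
- ANCOVA: 1-rho²

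ANCOVA relative to change score: (1-rho²)/[2(1-rho)] = (1+rho)/2. ANCOVA relative to ANOVA: 1-rho². Both ratios are below 1 for every 0 < rho < 1; ANCOVA spends one extra degree of freedom.

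**Step 3: power if eta-squared .11 is the two-time interaction effect.** ANCOVA has lambda = 8.157/[(1+rho)/2] on F(1, 65). The N column is the smallest total giving 80% power.

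| rho | variance ratio | lambda | power at N = 68 | N for 80% | saving from 68 |
|---|---|---|---|---|---|
| .5 | .75 | 10.88 | .90 | 52 | 16 |
| .6 | .80 | 10.20 | .88 | 55 | 13 |
| .7 | .85 | 9.60 | .86 | 58 | 10 |
| .8 | .90 | 9.06 | .84 | 62 | 6 |

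**Step 4: the 2 x 3 interaction on the same scale, F(2, 132).** If the effect is equal at both later occasions, lambda = 8.157 x 4/3 = 10.88 and power is .84. If it builds linearly to 3 months, lambda = 8.157 and power is .72. Against the first case the ANCOVA gain runs from .06 at rho .5 (.90 against .84) to about nil at rho .8 (.84 against .84).

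**Step 5: all four tests at one fixed effect.** Take a true 3-month difference of 0.5 SD at N = 68. The base noncentrality is 0.5² x 68/4 = 4.25, divided by the relevant variance for the 1-df tests. For the 2 x 3 test with equal effects at both later occasions it is 4.25/[1.5(1-rho)].

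| rho | later-score ANOVA | two-time interaction | 2 x 3 interaction | ANCOVA |
|---|---|---|---|---|
| .5 | .53 | .53 | .55 | .65 |
| .7 | .53 | .75 | .78 | .81 |
| .8 | .53 | .90 | .93 | .92 |

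**Step 6: effect of an open choice on type I error.** Null data were simulated with 34 per arm and 4,000 runs per correlation. Reporting the most favourable of ANOVA, change score and ANCOVA at 3 months, for one outcome, rejects in .095 of runs (rho .5) and .106 (rho .7). Adding the 2 x 3 interaction gives .118 and .129. Also allowing the three single-occasion tests at post-training gives .17 and .19. These rates apply only if the choice is made on the results.

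**The case against.** The best reply has four parts.

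- **ANCOVA is already on the list.** If the investigators use it, the change adds no precision. This stands; what remains is removing the choice.
- **The sentence may be shorthand.** It covers outcomes measured two or three times, an article condenses a fuller plan, and the comma may be a slip for repeated-measures ANOVA or ANCOVA. Even on that reading, two non-equivalent models remain for RRS and BDI-II, and neither is tied to baseline adjustment.
- **Occasion-specific comparisons are planned.** The follow-up t-tests do address post-training and 3 months separately, so it would be wrong to say the plan never yields a 3-month comparison. Nothing says these t-tests are baseline-adjusted.
- **Outcome analysis is blinded.** The Blinding section has the outcomes analysed under two uninformative labels. This limits choosing a model because it favours CCT, but a p-value below .05 is visible without knowing which arm is which.

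A reader might also infer more than the article supports:

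- That Design and Sample size contradict each other. They do not: powering one two-time interaction inside a three-occasion trial is permissible, and 68 reproduces.
- That the test will be picked after the data are seen. The article does not say so.
- That 3 months is the primary time point. Both occasions are to be tested and neither is ranked.
- That randomisation is unstratified. The Randomization section is silent on this, and the point does not depend on it.

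**Conclusion.** The point holds as a near-free improvement and is not an error in the sample size or the design. The listed tests differ, and baseline adjustment is not required where it would help. Against the two-time interaction that reproduces the planned 68, ANCOVA raises power from .80 to about .90 to .84 for rho .5 to .8, equivalent to 16 to 6 fewer participants. The direction of the variance advantage over the change score and the later-score ANOVA holds for all rho between 0 and 1; its size depends on a correlation that the documents do not give. Against the 2 x 3 interaction the gain depends on rho and on the shape of the effect, and may be near zero. If ANCOVA would be used anyway, the benefit is only a fixed test and protection of the 5% level.

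**What to change.** Replace the list with one model. For RRS and BDI-II, use ANCOVA of the outcome on condition with the same measure's baseline score as covariate, reporting the adjusted difference and 95% CI at post-training and at 3 months. CERQ, collected on the same three occasions, can follow this form. For QLDS, WHODAS 2.0, RS and RDQ, use the same model at 3 months. These adjusted contrasts replace the unadjusted follow-up t-tests. The 2 x 3 interaction may stay as a supporting analysis.

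The investigators should also state which time point is decisive. Three months fits the Discussion's aim of reducing vulnerability over 3.5 months, but the choice is theirs. Both statements should be fixed before unblinding, and preferably before the independent researcher releases the grouped subject list, since p-values can be computed from then on.

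The cost is wording plus that one decision. No new data are needed, N stays at 68, and the Trial status section says recruitment is still under way. The change does not settle the two primary outcomes, RRS total versus brooding, or the use of LOCF; those need their own decisions.

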These first experimental findings are in line with existing conceptual frameworks concerning the role of cognitive control and rumination in recurrent depression [6, 25], suggesting that by remediating cognitive control impairments, one might decrease cognitive vulnerability for future depression. Accordingly, Siegle et al. [20] have suggested that effects of CCT on depressive symptomatology are preceded by changes in rumination. However, to date no experimental study has directly tested this mediation effect. Furthermore, previous studies have typically explored curative effects of CCT in MDD patients whereas only more recently the preventive potential of CCT has been explored in student populations. For instance, in a single session cognitive control manipulation, Cohen et al. [26] have demonstrated that inducing cognitive control while processing negative information buffers against negative effects of a subsequent rumination induction procedure (i.e., state rumination, rumination-related sad mood). Moreover, training inhibition of emotional information has shown to reduce rumination in at-risk students [27]. Interestingly, researchers have found that the adaptive PASAT shows promise in reducing stress reactivity and rumination in response to a lab stressor directly following training and a naturalistic stressor at one month follow-up in an at-risk student sample [28]. Furthermore, decreased stress reactivity in confrontation with a lab stressor predicted lower brooding levels following confrontation with naturalistic stress (i.e., examination period). These findings suggest that CCT targeting working memory functioning shows potential as a preventive intervention for depression.

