### Rational for the proposed study

Previous studies indicate that the effects of CCT are not limited to the mere reduction of current depressive symptomatology in MDD patients, but might also extend to increasing resilience in at-risk populations. However, several theoretical gaps remain to be addressed.

First, in order to fully explore the potential of CCT targeting working memory functioning in reducing (cognitive) vulnerability for depression, a test of training effects in a RMD sample would be desirable. That is, RMD patients form a high-risk group for developing future depressive episodes [29] and prospective studies indicate that impaired cognitive control forms an important vulnerability factor in RMD [14]. Second, from a theoretical stance it would be interesting to explore the proposed mediational pathway from effects of CCT on rumination to reduced future depressive symptomatology. Third, with the exception of Siegle et al. [20] who explored effects of CCT on outpatient service use, previous studies have limited their scope to exploring effects of CCT on rumination and depressive symptomatology. We aim at extending previous findings by also exploring effects of CCT on adaptive emotion regulation as well as broader indicators of (dis-)functioning such as experienced disability, experienced remission from depression, and Quality of Life. Furthermore, we are not only interested in change in behavior indices of cognitive control, but also in the clinical experience of RMD patients concerning these cognitive factors (e.g., self-report measures of executive- and working memory functioning). Finally, in order to reduce sources of bias in exploring the potential of CCT as a preventive intervention, a rigid methodological approach — i.e., a double-blind randomized controlled trial (RCT) — is required.

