## Discussion

Prevention of recurrent depression is an important target for interventions. Previous findings indicate that CCT shows potential in reducing depressive symptomatology and rumination in MDD as well as cognitive vulnerability in at-risk undergraduate students. To test the potential of CCT as a preventive intervention for depression, the present study aims to test the effectiveness of CCT in a RMD sample. We will test whether CCT targeting working memory functioning — as compared to a low cognitive load training — can be used to reduce vulnerability for depression over a 3.5 months period. We hypothesize that CCT will have beneficial effects on primary outcome measures depressive rumination (i.e., brooding) and depressive symptomatology and hope to see these findings extend to adaptive emotion regulation and long-term functioning (secondary outcome measures).

This double blind RCT study forms a first test of the potential of CCT as a preventive intervention for depression in RMD. Furthermore, these findings will be informative to the literature as several exploratory questions will be addressed in order to further elucidate the role of cognitive control in vulnerability for depression. First, we will explore whether effects of CCT on depressive symptomatology are mediated by rumination. Second, we will explore whether effects of CCT extend to measures of adaptive emotion regulation and indices of functioning such as quality of life and disability. Third, in order to further elucidate the mechanisms involved during CCT, we could explore how process measures of CCT relate to effects of training.

Overall, this study will further enhance the knowledge on the role of cognitive control in emotion regulation and vulnerability for depression. This study forms a first step in testing the effectiveness of CCT targeting working memory functioning as a preventive intervention for (recurrent) depression. If these first results show to be promising, future work should focus on replicating the effects of CCT and exploring how this preventive intervention could best be implemented.

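### The only mediation analysis specified is within-group, so it cannot estimate whether the effect of CCT on depressive symptoms runs through rumination

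*Protocol article*

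**What the plan says.** The rationale section sets the aim to "explore the proposed mediational pathway from effects of CCT on rumination to reduced future depressive symptomatology". The Discussion lists it first among the exploratory questions: "we will explore whether effects of CCT on depressive symptomatology are mediated by rumination". The Background gives the reason for asking: "However, to date no experimental study has directly tested this mediation effect".

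The method appears in a single sentence of the Analysis section: "Explorative within-group mediation analysis will be performed using a stepwise regression approach", together with a bootstrapping method. The predictor, mediator, outcome and time points are not named, and *within-group* is not defined. No mediation model with condition as the independent variable appears anywhere in the article.

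The design would support such a model: "We present a 2 (Condition) x 3 (Time) double blind, randomized controlled design". Table 1 schedules the RRS and BDI-II at baseline, post-training and three months in both arms.

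**The concern.** The question concerns the effect of CCT, that is, CCT compared with the low-load control. It has two parts: whether allocation to CCT changes rumination, and whether that change carries through to later depressive symptoms. Only the comparison of the randomised arms informs the first part, and the within-group specification leaves that comparison out.

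What remains is an association between two self-report scales, or between a training measure and those scales. Such associations also arise from natural course, regression to the mean and shared reporting style. The article presents the trial as an experimental test of a pathway that earlier work had not tested directly. If the within-group result is reported in answer to that question, readers may take an observational association for the missing experimental evidence.

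**Working it through.** **The plan's own figure.** The plan gives no number for the mediation analysis. Its sample size matters because it fixes how many people each approach uses.
- Inputs (Sample size section): η² = .11, α = .05, power .80, total 68, 34 per arm.
- f = √(.11/.89) = 0.352; d = 2f = 0.703.
- Two-group F-test with noncentrality N·f²: N = 66, and power at N = 68 is 0.815. With noncentrality f²(N − 2), N = 68 exactly. The stated 68 is reproduced.

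**What each reading of *within-group* can estimate.** Let X be the predictor, M rumination and Y depressive symptoms. The indirect effect is a·b, where a is the effect of X on M and b is the effect of M on Y given X.
1. *One arm only.* Condition is constant, so a for condition does not exist. X must be something unrandomised, such as training performance or change in cognitive control. Suppose CCT lowers everyone's rumination by the same amount δ. Then cov(X, M + δ)/var(X) = cov(X, M)/var(X), so δ drops out of every within-arm slope. If the effect of CCT varied with X, the slope would pick up part of it, but without the control arm that part cannot be separated from a pre-existing association.
2. *Within-person change.* Mean change in the CCT arm is natural course plus δ. The two cannot be separated without the change in the control arm.

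Neither reading contains the contrast that the question needs.

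**Illustration by simulation.** Assumed, not from the documents: 34 per arm; M affects Y with slope 0.5 in SD units; within an arm, X correlates .3 or .5 with M through a common cause only; mediation is declared when paths a and b are both significant at two-sided .05.

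| CCT effect on M | Corr(X, M) | Within CCT arm (n = 34) | Condition as X (N = 68) |
|---|---|---|---|
| none | .3 | 31% | 5% |
| none | .5 | 66% | 6% |
| d = 0.703 | .3 | 35% | 79% |
| d = 0.703 | .5 | 66% | 81% |

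These are from 3,000 runs per row. The gap between 31% and 35% is simulation noise. A rerun with 15,000 runs, using the same draws with and without the CCT effect, gave 34% in both cases at correlation .3 and 66% in both at .5, as the algebra requires. Condition as X then gave 5% and 81%. The last figure agrees with the 0.815 power for path a computed above, since path b is almost always detected at N = 68.

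**The case against.** The strongest reply is that the sentence may not be aimed at this question. *Within-group* is undefined, and the article has process questions that belong naturally inside the CCT arm, such as how training measures relate to training effects (Discussion, Blinding). A full mediation model may also sit in a longer protocol that is not shown. This stands as a reason not to be dogmatic about the intended reading. It does not remove the mismatch: the article fixes a within-group form, it is the only mediation analysis described, and neither reading supplies the randomised contrast.

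A second reply is that between-condition intention-to-treat tests of the RRS and BDI-II are planned and the mediation is labelled exploratory. That is correct and limits the damage. A reader might infer that the trial would announce a mechanism even if CCT did nothing. The article does not support that, because a null between-condition result would be reported alongside. Those tests do give the effect of CCT on rumination, but no planned step combines it with the rumination-to-depression path.

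A reader might also infer that the stepwise regression is itself a defect. The article does not say what its steps require, and a bootstrap is planned with it, so no criticism of the stepwise method is made here.

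**Conclusion.** The specified analysis does not match the stated question. Without condition as the independent variable, neither the effect of CCT on rumination nor the indirect effect can be estimated, so a within-group association could be misread as a mechanism. This follows from the structure of the analysis under either reading of *within-group* and needs no assumed figures. The simulated percentages rest on assumed correlations and a joint-significance rule. They illustrate the problem and do not forecast how often this trial would go wrong.

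The point is of moderate weight. It affects an exploratory aim that the article nevertheless puts forward as a gap to be filled. It does not touch the primary or secondary efficacy comparisons.

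**What to change.** In the Analysis section, specify for this question a model along these lines:

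*Exploratory mediation of the effect of condition by rumination will be estimated in the full randomised sample. X is randomised condition. M is post-training rumination on the RRS, with the score fixed in advance, adjusted for its baseline. Y is BDI-II at three months, adjusted for baseline BDI-II and baseline rumination. The indirect effect will be reported with a bootstrap 95% confidence interval. Within-group results will be labelled descriptive associations.*

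Brooding is a natural candidate for the RRS score, since the Discussion names it in the hypothesis. What matters is that one score is chosen beforehand.

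Add that rumination is not itself randomised, so the rumination-to-depression path assumes no unmeasured mediator-outcome confounding, even with condition as X. Keep the analysis exploratory. If the sponsor prefers only within-group analyses, the aim in the rationale and Discussion should be narrowed to match.

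The cost is wording only. The measures are already scheduled in both arms, the bootstrap is already planned, and up to 68 participants contribute instead of 34. The model can be run on the two non-informative group labels described under Blinding, so blind evaluation is preserved.
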